#### 2.6.2. tDCS Simulation

The GUI based Software ‘Neurophet tES LAB 3.0’ that can calculate the tDCS-induced electrical fields after considering an individual’s brain structure by analyzing and segmenting the T1-weighted MR image of the individual participant, is applied in this trial to plan the tDCS protocol. Following enrollment, each participant’s T1-weighted MR images, taken at the baseline, are analyzed in the software, of the skin, skull, brain tissues (cerebral gray and white matter, cerebellum gray and white matter, cerebrospinal fluid, ventricle) and the affected tissue; a region affected by stroke and not fully replaced with CSF, are segmented in the software, based on an electrical conductivity. At this time, for the segmentation of the whole brain tissue, including the stroke-affected tissue, a U-Net structure, i.e., an encoder-decoder based network, is used. Given a T1-weighted MR image as input to the network, the encoder first extracts the feature from the input image. The features are then provided to a decoder network, and during the decoding process, the decoder network reconstructs the features to the original image size [28]. Then, the investigators could modify the results of the tissue segmentation, including the affected tissue. We set the electrical conductivity of eight tissues as follows: skin, 0.465; skull, 0.010; cerebral and cerebellar gray matter, 0.265; cerebral and cerebellar white matter, 0.126; CSF and ventricle, 1.65; and affected tissue 0.08089. The principal investigators will confirm the segmented results, and all procedures are applied to all participants, according to the same rules. Following segmentation, a 3D brain model of each participant is created. An investigator selects the landmarks, including nasion, inion and the right and left preauricular points in the model. The next steps are continued, based on the randomized groups.

##### Opt-tDCS Group (Personally Optimized tDCS; Experimental Group)

The investigator selects a target that represents the structural M1 representation of the hand in the cerebral gray matter of the participant’s hemisphere with the lesion. Next, the investigator attaches the anode electrode directly above the target, and the cathode electrode at the position representing M1 in the contralesional hemisphere. These electrode locations are the initial locations for the tDCS optimization calculations. Based on the locations, the two electrode locations that can maximally stimulate the M1 target in the frontal area of the participant’s ipsilesional and contralesional hemispheres are chosen. At this time, the investigators input the tDCS simulation parameters, such as the current intensity (2 mA), electrode type (5 × 5 square type), and conductivity of the brain tissue, to calculate the optimal electrode locations. The volumes of all segmented layers generated the 3D brain model, and the simulation calculated the magnitude of the electric field generated by tDCS, through the brain structure. By applying the optimized tDCS simulation to the patients, the simulation finds the combination of the tDCS electrodes to generate the maximum electric fields or the maximum inward electric field values in the region of interest. Among the several location candidates, when the combination of the electrode locations that can maximally stimulate the target is calculated, medical device investigators find the corresponding electrode position, based on their landmarks and start the tDCS.

##### Con-tDCS Group (Conventional tDCS Based on a 10–20 EEG System.; Active Control Group)

As with the opt-tDCS group, the investigators created a 3D brain model for each participant and selected the landmarks for the tDCS electrode location generation in tES LAB software. Then, the software automatically generates the locations, according to a 10–20 EEG-based system in the software. For this group, the electrode positions are selected, according to the 10–20 EEG system, an anode electrode is attached to the ipsilesional side (C3 or C4), and a cathode electrode is attached to the contralesional side.

##### Sham-tDCS Group

Simulations for the sham-tDCS group were performed with the same procedure as for the opt-tDCS group; therefore, the electrode locations were the same as that group, but during the tDCS stimulation, the ‘sham mode’ was applied for the initial and final 1-min periods with a ramping up and down for 30 s.

### 2.7. Blinding

In the case of this study, it is difficult to keep the examiner blinded because the location of the tDCS electrodes is different, depending on the treatment method. Therefore, an unblind investigator, in charge of the application of medical devices for clinical trials, is separately assigned to each site, to maintain the blindness of the blinder. The unblinded investigator does not participate in the research process other than the treatment to minimize the impact on the efficacy and safety evaluation of the investigator, due to an unblinded design.

### 2.8. Primary Outcome

Upper limb functional changes will be evaluated by the FMA-UE scores, between the baseline and postintervention, at 2 weeks. The FMA-UE is a performance-based impairment index, including the motor function with a range of motion and sensation in patients with a stroke, and the results are represented as a numerical score with a maximum of 66 points [27,29].

### 2.9. Secondary Outcomes

The secondary outcomes include the changes in the motor evoked potentials (MEPs); frequency power and coherence of electroencephalography (EEG); upper extremity functions; Wolf motor function test (WMFT) [29,30], box and block test (BBT) [31], performance in activities of daily living (ADLs) [32], and adverse events with the 1-month follow-up assessment (for details, see Table 1).

### 2.10. Sample Size Estimates

Most studies that aimed to assess the efficacy of the MRI-driven optimized tDCS, were retrospective computational studies or case reports [26]. Moreover, this trial is the first to report the efficacy of the optimized tDCS on the upper limb functions in stroke patients. Considering that there were no prior data on the effects of the optimized tDCS, using an MRI-driven tDCS-induced electrical field calculation simulation on stroke patients, we estimated that enrolling 42 patients, considering a dropout rate of 10% for each group, would be a reasonable approach for an exploratory trial.

### 2.11. Statistical Analyses

The descriptive statistics (average, standard deviation, median, minimum, and maximum) are presented for each group for the change in the primary outcomes at 2 weeks, compared to the baseline (0 weeks), and the comparison of differences between the groups will be the repeated measures ANCOVA that considers time as a covariate. If statistically significant changes were confirmed in the comparison of the differences between the three groups, a repeated ANCOVA that considered the timing of the differences between the two groups (e.g., opt-tDCS and con-tDCS, opt-tDCS and sham-tDCS) was planned as a post hoc analysis. The results corresponding to the secondary outcomes will be presented as descriptive statistics (frequency, ratio) for each group, based on the change in score at 4 weeks, and the difference between the two groups, will be analyzed using the repeated measures ANCOVA, that considers time.

The primary outcome will be analyzed in the intention-to-treat population, and the safety outcomes will be analyzed in the per-protocol population. No protocol interim analysis is planned, and a total of 42 patients will be enrolled in this clinical trial over a total of 30 months. This sample will be able to evaluate the clinical applicability of the optimized tDCS treatment in the subacute to chronic stages of a stroke and aims to verify the trends in the intergroup differences and the changes to demonstrate the statistically significant differences in the upper limb function improvement between the two groups.

The outcome analysis of this trial will be largely divided into a safety set (SS) group, a full analysis set (FAS) group, and a per-protocol set (PP) group. The efficacy evaluation will analyze the PP group as the main analysis group and analyze the FAS group. If the results are different across the analysis groups, the results of each analysis method will be presented and analyzed to identify the reason. The safety assessment will be carried out in the SS group, and the significance level will be set at 0.05.

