## Abstract

Transcranial direct current stimulation (tDCS) has been shown to have the potential to improve the motor recovery of the affected upper limbs in patients with stroke, and recently, several optimized tDCS methods have been proposed to magnify its effectiveness. This study aims to determine the effectiveness of personalized tDCS using brain MRI-based electrical field simulation and optimization, to enhance motor recovery of the upper limbs in the patients. This trial is a double-blind, randomized controlled trial in the subacute to chronic rehabilitation phase. Forty-two adult stroke patients with unilateral upper limb involvement will be randomly allocated to three groups: (1) personalized tDCS with MRI-based electrical field simulation and optimized stimulation, (2) conventional tDCS with bihemispheric stimulation of the primary motor cortex, and (3) sham tDCS. All three groups will undergo 10 intervention sessions with 30 min of 2-mA intensity stimulation, during a regular upper limb rehabilitation program over two weeks. The primary outcome measure for the motor recovery of the upper limb impairment is the Fugl–Meyer assessment for the upper extremity score at the end of the intervention, and the secondary measures include changes in the motor evoked potentials, the frequency power and coherence of the electroencephalography, performance in activities of daily living, and adverse events with a 1-month follow-up assessment. The primary outcome will be analyzed on the intention-to-treat principle. There is a paucity of studies regarding the effectiveness of personalized and optimized tDCS that considers individual brain lesions and electrical field characteristics in the real world. No feasibility or pivotal studies have been performed in stroke patients using brain MRI, to determine a lesion-specific tDCS simulation and optimization that considers obstacles in the segmentation and analysis of the affected brain tissue, such as ischemic and hemorrhagic lesions. This trial will contribute to addressing the effectiveness and safety of personalized tDCS, using brain MRI-based electrical field simulation and optimization, to enhance the motor recovery of the upper limbs in patients with stroke.

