### 2.4. Inclusion and Exclusion Criteria

The *inclusion criteria* are as follows: (1) age over 19 years old; (2) stroke confirmed by brain MR images; (3) first-onset stroke; (4) subacute or chronic phase (at least 4 weeks after the stroke onset); (5) unilateral upper limb paralysis; (6) an upper extremity FMA score (out of 66) of 56 or less; and (7) capacity to understand the explanation of this clinical trial, voluntary participation and written agreement to abide by the precautions.

The exclusion criteria will be the following: (1) those with a disease that may affect the function of the paralyzed arm, such as recurrent stroke, traumatic brain injury, spinal cord injury, degenerative brain disease, such as Parkinson’s disease, or upper extremity nerve injury; (2) those who cannot conduct clinical trials according to the instructions, due to cognitive decline; (3) those who have severe communication difficulties, due to total aphasia; (4) those with evidence of delirium, confusion or other disturbances of consciousness; (5) those with an uncontrolled medical or surgical disease; (6) those who cannot undergo tDCS due to scalp disease; (7) those who have metallic substances (e.g., clip, coil, or metabolic foreign body) in the brain; (8) those with pacemakers or cochlear implants; (9) those who have used stimulation devices that are similar to the medical devices used in this clinical trial, within at least 1 year, or have experience in participating in related clinical trials; (10) those with severe neurological disorders accompanying major psychiatric disorders; (11) those with a history of epilepsy; (12) those who have medical contraindications to brain imaging acquisition; (13) those who have taken prohibited concomitant medications or need to change medications that may affect their cognitive and motor function changes, through changes in brain activation during the study period (however, this does not apply to those who are taking the drug in a stable manner); and (14) pregnant or lactating women and those who plan to become pregnant during the clinical trial period.

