### 2.5. Enrollment and Randomization

Participants who meet all the inclusion criteria and none of the exclusion criteria and have given informed consent, will be evaluated by the investigators for enrollment. At enrollment, the information will be collected, including the demographic data, body measurements, stroke history, complications, and baseline function measures. The investigator will verify that the patient is eligible to participate and enter information into the electric data capture and web allocation system, as required.

The participants will be randomly assigned to a personally optimized tDCS group (opt-tDCS), a conventional tDCS group (con-tDCS; an active control group), or a control group (sham-tDCS) in a 1:1:1 ratio, in the order of registration. To minimize the effects, based on the disease severity, a Fugl–Meyer assessment for the upper extremities (FMA-UE) cutoff values were used to divide patients into 0–34 (moderate to severe) and 35–56 (mild to moderate) groups, and the onset period was used to stratify patients into two groups, subacute (onset 1–6 months) and chronic (greater than 6 months). Statisticians who were not otherwise involved in this clinical trial used statistical software to randomize the randomization numbers, according to the block randomization method. The issued randomization number was put in a randomization bag and delivered to the medical device manager of each site. The allocation sequence was concealed from an independent researcher. A sealed envelope was given to the coordinator of the physical therapy area to identify the group for each participant.

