### 2.6. tDCS Treatment, Simulation and Blinding

#### 2.6.1. tDCS Device

Participants will undergo an intervention tDCS treatment using a battery-driven and portable device (Neurophet innk, Neurophet, Seoul, Republic of Korea), programmed to deliver either active or sham tDCS. The device delivers 2.0 mA (with 30 s for ramping up and ramping down; Figure 2) of the direct current through the two sponge-coated electrodes (electrode size: 5 × 5 cm^2^). The tDCS device used in this study can check the impedance values occurring in patient’s skin, in real time, during all tDCS sessions. If an impedance above 13 kOhm occurs, the stimulation is stopped, and the medical device investigator confirms the patient’s condition and skin. This may reduce the adverse events that may occur on the patient’s skin, due to the increased impedance. In the sham-tDCS condition, the device delivers 120 s of the current, including 30 s for ramping at the beginning and end of each session, to maintain the blinding procedure. The tDCS treatment was performed 10 times over a total of 2 weeks, and sham-tDCS was also applied 10 times with sham stimulation for 2 weeks. Following this duration, both opt-tDCS and con-tDCS groups, but not the sham-tDCS group, will receive the opportunity to provide additional written consent for an extension study; if the participants give consent, the extension study will be conducted for two additional weeks. During the 2 or 4 weeks of intervention, if there was a usual rehabilitation program that was being performed before participation in this study, the program and frequency could be continued without any changes. The detailed intervention methods regarding tDCS for each group, is as follows (Figure 3a). The representative figure which represents the difference between optimized tDCS and conventional tDCS simulation results in participant is Figure 3b.

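### As written, the primary model names time as its only covariate, although the primary outcome has one post-baseline time, and specifies neither the 2-week contrast nor adjustment for baseline FMA-UE.

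*Protocol article*

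**What the plan says.** Section 2.8 defines the primary outcome as a change over one interval: "Upper limb functional changes will be evaluated by the FMA-UE scores, between the baseline and postintervention, at 2 weeks". The Abstract gives it as "the Fugl–Meyer assessment for the upper extremity score at the end of the intervention". Both imply one post-baseline value per patient, which Table 1 places at V12.

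Section 2.11 summarizes each group "for the change in the primary outcomes at 2 weeks, compared to the baseline (0 weeks" and then fixes the test: "the comparison of differences between the groups will be the repeated measures ANCOVA that considers time as a covariate". If the three-group comparison is significant, pairwise comparisons follow, using "a repeated ANCOVA that considered the timing of the differences between the two groups". The same type of model is planned for the secondary outcomes, on the change at 4 weeks.

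Baseline FMA-UE is used in the design. Eligibility requires "an upper extremity FMA score (out of 66) of 56 or less", and the randomization is stratified: "cutoff values were used to divide patients into 0–34 (moderate to severe) and 35–56 (mild to moderate) groups". The second stratification factor is onset phase, subacute or chronic. Section 2.11 names neither baseline FMA-UE nor the stratification factors as covariates.

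**The concern.** Repeated measures need at least two response times, and time is informative as a covariate only if it varies within the analysis. With one post-baseline time, the model sentence does not say what the response is or which coefficient is tested. The one coefficient suggested by a group comparison adjusted for time is the group main effect, and over baseline and 2 weeks that is not the 2-week difference.

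The sentence governs the primary test. In Section 2.11 the pairwise comparisons of optimized tDCS with conventional and with sham tDCS depend on that test being significant, so a test aimed at the wrong coefficient could block the comparisons the trial was set up to make. Separately, a covariate that every patient has, and that was thought important enough to stratify on, does not enter the model as a covariate.

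**Working it through.** The article gives no power calculation, effect size, SD or correlation, so there is no planned figure to reproduce.

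**Inputs from the article:** 42 patients allocated 1:1:1, hence 42/3 = 14 per arm (Sections 2.5 and 2.10); significance level 0.05 (Section 2.11); assessments at 0 and 2 weeks.

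**Assumptions:** equal SD σ at both times; baseline/2-week correlation ρ of 0.7 to 0.95; optimized tDCS better than both controls by δ = 1 SD of change; no difference between the controls.

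**What each reading estimates**

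1. Raw scores, group plus time. The group term is the difference in patient means over the two times: (baseline difference + 2-week difference)/2. Randomization makes the expected baseline difference zero, so it estimates δ/2, with per-patient variance σ²(1+ρ)/2.
2. Change as response. Each patient has one value and time is constant, so it drops out. What remains is a one-way ANOVA on change, with variance 2σ²(1−ρ).
3. Raw scores with group-by-time. With two times, the interaction equals the difference in mean change, the same estimate as reading 2.
4. For comparison, ANCOVA of the 2-week score on group and baseline, with variance σ²(1−ρ²).

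A two-arm simulation (14 per arm, assumed SD 12, true 2-week difference 5 points, 10,000 runs at each of ρ = 0.7, 0.9 and 0.95) gave mean estimates of 2.54 to 2.56 for reading 1, 4.98 to 5.01 for readings 2 and 3, and 4.99 to 5.04 for ANCOVA. A random-intercept mixed model fitted to one data set confirmed the identities in 1 and 3.

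**Power of the three-group F test.** Arm means 1, 0, 0 in SDs of change have a sum of squares about their mean of 2/3. The noncentrality is therefore:

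- change score: 14 × 2/3 = 9.33
- group main effect: 9.33 × (1−ρ)/(1+ρ), which is 1.65 at ρ = 0.7 and 0.49 at 0.9
- ANCOVA: 9.33 ÷ [(1+ρ)/2], which is 10.98 at 0.7 and 9.82 at 0.9

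The numerator has 2 degrees of freedom; the error has 39 (38 for ANCOVA).

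| ρ | group term, raw scores | change score or group-by-time | ANCOVA on baseline |
|---|---|---|---|
| 0.70 | 0.181 | 0.752 | 0.821 |
| 0.80 | 0.129 | 0.752 | 0.797 |
| 0.90 | 0.086 | 0.752 | 0.774 |
| 0.95 | 0.067 | 0.752 | 0.763 |

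With 12 evaluable per arm (inferred from 10% dropout, not stated), the ranges over the same ρ are 0.159 to 0.064, 0.675, and 0.748 to 0.685.

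**Cost of not adjusting for baseline.** The ANCOVA to change-score variance ratio is σ²(1−ρ²) ÷ 2σ²(1−ρ) = (1+ρ)/2: 0.85 at ρ = 0.7 and 0.95 at 0.9. The change score then needs 1/0.85 = 1.18 or 1/0.95 = 1.05 times as many patients for the same precision.

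**A later visit does not supply the repeated measure.** Table 1 places V23 after the extension, and Section 2.6.1 says that "both opt-tDCS and con-tDCS groups, but not the sham-tDCS group, will receive the opportunity to provide additional written consent for an extension study".

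**The case against.** The article does not say that the group main effect will be tested. Section 2.8 defines the outcome as a change, the model sentence follows directly on a summary of the change at 2 weeks, and the pairwise step speaks of the timing of the differences. This wording supports a change-score or group-by-time analysis at least as well, and either is unbiased under randomization. This stands, and it limits the finding: the halved effect and the severe loss of power belong to one reading only.

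A reader might go further and infer that the model cannot be fitted. It can: with change as the response, time drops out and a one-way ANOVA remains. A reader might also infer that baseline FMA-UE is ignored altogether. It is not: it is subtracted in the change score and is a response value in the raw-score models. It is missing only as a covariate, which costs precision and not validity, and stratification by FMA-UE band limits chance imbalance.

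It can also be said that this is an exploratory feasibility study, reported in an article that may leave covariate lists to an analysis plan. That would excuse silence, but here the article fixes the covariate and fixes it as time. Section 2.11 also makes the pairwise tests depend on significance and aims to show statistically significant differences, so power matters.

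**Conclusion.** The point holds for the model as written. The primary test is stated in a form that does not fit an outcome with one post-baseline time and that leaves the tested coefficient open. Under the assumptions above, the admissible readings range from 18% power or less (9% at a correlation of 0.9) to about 75%. The halving of the effect in the literal reading depends on neither the assumed effect size nor the correlation; the power figures depend on both.

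If the authors intend a change-score or group-by-time analysis, what remains is a modest loss: power of 75% against 82% at a correlation of 0.7, or 77% at 0.9. The documents do not support the stronger conclusion that the trial will estimate the wrong quantity. This should be fixed, but it is a defect of specification and not a demonstrated wrong analysis.

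**What to change.** Replace the model sentence in Section 2.11 with:

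> FMA-UE at 2 weeks (V12) will be compared between groups by ANCOVA with treatment group as factor and baseline FMA-UE as continuous covariate, adjusting for the stratification factor of onset phase; adjusted mean differences with 95% CIs will be reported.

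Use the same model for the pairwise comparisons. The FMA-UE band need not be added, because the continuous baseline score carries it.

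For continuous secondary measures at 2 weeks, use the same model with each measure's own baseline. Do not extend it to adverse events, which Section 2.9 lists among the secondary outcomes, or to a three-arm comparison at 4 weeks, because the sham group is not offered the extension.

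The cost is wording, plus one degree of freedom for baseline and one for onset phase. No new data are needed: baseline and V12 functional examinations are already in Table 1, and onset phase is recorded for stratification.

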Taking into account the mentioned limitations of the conventional tDCS method and the results of a previous study, our ongoing development of optimized software, and current clinical demands, we hypothesized that MRI-based optimized personalized tDCS would be better than conventional tDCS, to treat patients with a stroke for improving the upper limb function. Thus, we will investigate the efficacy of the MRI-based optimized personalized tDCS for improving the upper limb function in patients with a subacute and chronic stroke via a multicenter prospective randomized double-blinded controlled trial. We present the rationale and precise methods from our planned trial: MRI-based personalized transcranial direct current stimulation to enhance the upper limb function in patients with a stroke: A randomized double-blinded controlled trial. The proposed protocol seeks to establish the benefits from personalized anodal tDCS with two control groups, a sham control group and a conventional anodal tDCS group, to prove the treatment efficacy of the upper limb motor function in patients with a stroke.

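### The model-based estimate of the hypothesised contrast, optimised versus conventional tDCS, is produced only if a three-group test is significant, so it is reported selectively

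*Protocol article*

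**What the plan says.** The Introduction gives a directional hypothesis about two arms: "we hypothesized that MRI-based optimized personalized tDCS would be better than conventional tDCS". The same section, and 2.1 Trial Design, also name sham as a comparator.

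Section 2.11 analyses the primary outcome, FMA-UE change at 2 weeks, in two stages. The three arms are first compared by repeated measures ANCOVA. Then comes the condition: "If statistically significant changes were confirmed in the comparison of the differences between the three groups, a repeated ANCOVA that considered the timing" is applied to differences between two groups. The pairs appear as examples, without ranking: "e.g., opt-tDCS and con-tDCS, opt-tDCS and sham-tDCS) was planned as a post hoc analysis". On alpha, the section says only that "the significance level will be set at 0.05". It states no sidedness.

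Descriptive statistics of the primary change (mean, SD, median, range) are to be shown for each group, with no condition attached.

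On purpose, 2.10 says that "we estimated that enrolling 42 patients, considering a dropout rate of 10% for each group, would be a reasonable approach for an exploratory trial" and gives no effect size, SD or power. The aim in 2.11 includes looking at trends, but also "to demonstrate the statistically significant differences in the upper limb function improvement between the two groups".

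**The concern.** The hypothesis concerns opt against con, but the first test asks whether any of three arms differ. Whether the hypothesised contrast is then modelled depends partly on the sham arm, which that hypothesis does not mention. Two consequences follow.

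- **Selective reporting.** The model-based opt minus con estimate appears only in trials where the three arms happened to spread enough. If opt truly exceeds con, the estimates that appear are too large on average.
- **Mismatch of purpose.** A feasibility trial mainly owes its successor an unselected estimate and interval for the key contrast. A significance gate, with an aim phrased as demonstrating significance between two groups, does not serve that purpose.

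At stake is the figure from which a later trial would be sized. The article states the gate as a rule, so this is not a detail left to an unseen SAP.

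**Working it through.** **The plan's own figure.** Section 2.10 gives 42 patients, and 2.5 allocates them "in a 1:1:1 ratio, in the order of registration", so 42/3 = 14 per arm. With 10% dropout, 14 × 0.9 = 12.6, or about 12 evaluable. In the other direction, 12/0.9 = 13.3, rounded up to 14. The dropout arithmetic is consistent. There is no power calculation to reproduce.

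**Assumptions.** Normal outcome in SD units of the analysed change, equal SDs, two-sided 0.05, and true arm means chosen by me. A one-way F test stands in for the ANCOVA. Baseline adjustment would make a given difference larger in residual SD units.

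**Chance that the gate opens.** With n per arm and arm means m1, m2, m3 around their average m, the noncentrality is λ = n × Σ(mi − m)². The gate probability is P(F > F_crit) for noncentral F with 2 and 3n − 3 degrees of freedom. At n = 14 this is F(2, 39), with F_crit = 3.238.

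- Opt/con/sham = 0.5/0/0: Σ = 0.333² + 2 × 0.167² = 0.167, λ = 2.33, probability 24%.
- 0.8/0/0: λ = 5.97, 55%.
- 1.0/0.5/0: Σ = 0.25 + 0 + 0.25 = 0.50, λ = 7.00, 62%.
- 1.3/0.5/0: Σ = 0.49 + 0.01 + 0.36 = 0.86, λ = 12.04, 86%.
- 0.8/0.8/0: λ = 5.97, 55%, although opt minus con is zero.

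**Estimate and power.** Simulation (100,000 trials per scenario) agrees with these probabilities and gives the mean opt minus con estimate when the gate is open. Power is for a two-arm t test, run always or only after the gate.

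| Opt/con/sham (SD) | True opt − con | Gate opens | Mean estimate if open | Ratio | Power, always tested | Power, gated |
|---|---|---|---|---|---|---|
| 0.5/0/0 | 0.5 | 24% | 0.87 | 1.74 | 25% | 18% |
| 0.8/0/0 | 0.8 | 55% | 1.02 | 1.27 | 53% | 45% |
| 1.0/0.5/0 | 0.5 | 62% | 0.61 | 1.21 | 25% | 23% |
| 1.3/0.5/0 | 0.8 | 86% | 0.86 | 1.07 | 53% | 52% |
| 0.8/0.8/0 | 0 | 55% | 0.00 | none | 5% | 5% |

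Using the pooled three-arm error raises always-tested power slightly (54% at 0.8 SD). For the four rows with a true opt − con difference, the gate therefore costs about 1 to 9 points. With 12 per arm and con equal to sham, it opens in 21% of trials at 0.5 SD and 48% at 0.8 SD.

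**What 14 per arm can detect.** The difference detectable with 80% power is about (1.960 + 0.842) × √(2/14) = 1.06 SD by the normal approximation, and 1.10 SD by the noncentral t. At 12 per arm the latter is 1.20 SD.

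**The case against.** The case for the plan has weight.

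- **An estimate exists without the gate.** Group means and SDs are reported unconditionally, so a raw opt minus con difference and interval can be derived. A reader might infer that a non-significant three-group test leaves no estimate at all; the documents do not support that. Only the model-based comparison is withheld.
- **The gate need not usually stay shut.** That reading holds for small to moderate opt minus con differences with con close to sham. It fails at 0.8 SD, or when con clearly beats sham. The document gives no effect size that would settle it.
- **Inflation is not universal.** Across the scenarios run, it ranges from none (opt equal to con) to about 2.5 times (0.3 SD, con equal to sham, 12 per arm). Selecting on significance at this sample size inflates anyway: at a true 0.5 SD with con equal to sham, significant results average 1.9 times the truth without the gate and 2.0 times with it.
- **The gate controls error.** An overall test before pairwise tests is a standard device with three arms. Under the global null with 12 per arm, at least one of the two opt comparisons is significant in 4.2% of trials with the gate, against 9.1% with neither gate nor adjustment. Dropping it without a replacement would be wrong.
- **Sham is also a named comparator.** Making opt versus con the only test is therefore partly a preference. Nor does the text say that the third arm is dropped from the pairwise models.

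All of this narrows the point. None of it explains why the model-based estimate of the hypothesised contrast should depend on a three-group result.

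**Conclusion.** The concern holds in a limited form. The plan makes the model-based opt minus con estimate conditional on a test that does not match the hypothesis, so that estimate is reported selectively. The harm is largest when con is near sham and the true difference is moderate. It is small when con clearly beats sham, and the upward bias disappears when opt equals con. These sizes rest on assumed effects, a normal outcome with equal SDs, and a two-sided 0.05.

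The gate is not the main cause of low power; 14 per arm is. The case for change rests on matching the analysis to the hypothesis and on reporting an unselected adjusted estimate. The change is worth making because it is specific and nearly free.

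**What to change.** In 2.11:

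1. Estimate opt minus con and opt minus sham at 2 weeks from the one three-arm ANCOVA, and report both with 95% CIs whatever the three-group test shows.
2. To keep error control without the gate, pre-specify a fixed order: opt versus con first at two-sided 0.05, then opt versus sham at the same level only if the first is significant. Make con versus sham and the three-group test descriptive.
3. Reword the aim of demonstrating significant differences as estimating the differences with their precision, in line with the exploratory purpose in 2.10.

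The cost is protocol and SAP wording, settled before unblinding. No patients, visits or data are added. The downsides are that con versus sham loses formal testing, and that opt versus sham is formally tested only if opt versus con is significant. At this sample size the second restriction will often bind, which is why both intervals should be reported unconditionally.
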